### Primary outcome

Effectiveness of pain relief from randomisation to arrival at hospital as measured by Sum of Pain Intensity Difference (SPID) score (using a 0–10 numerical rating scale(NRS). As this is a pragmatic trial, no fixed time interval was specified to record pain scores, however we did request that pain scores were documented regularly from the point of initial IMP administration to arrival at the hospital.

### Secondary outcomes

*Effectiveness of pain relief and overall patient experience from randomisation to arrival at hospital*
Total Pain Relief (TOTPAR) scoreTime to perceptible analgesiaTime to meaningful analgesiaTime to peak analgesiaDuration of analgesiaRequirement for rescue analgesiaProportion of patients with a pain intensity score below 4/10 (0–10 numerical rating scale (NRS)) on arrival at hospitalVital signs (oxygen saturation, blood pressure, heart rate, respiration rate, Glasgow Coma Scale)Patient Global Impression of Change on arrival at hospital

*Incidence of side effects and adverse events*
Airway: vomiting, aspiration, advanced airway managementRespiratory: desaturation, need for ventilatory supportCardiovascular: arrhythmia, hypotension and hypertensionNeurologic: sedation, excitatory movements, adverse behavioural reactionsOther: nausea, allergic reaction

*Resource use*
Ambulance job cycle time (scene arrival to arrival at hospital)Number of ambulance resources (technicians, paramedics, doctors and vehicles) in attendanceCumulative IMP doses administeredCT scan useHospital or ICU admissionLength of stay ED, ICU, Hospital

*Longer term outcomes*
Chronic pain using Brief pain inventory-short form (BPI-SF) at 3 & 6 months from randomisationHealth-related quality of life measured using the EQ-5D-5L at 3 and 6 months from randomisationCost-effectiveness expressed in terms of incremental cost per quality-adjusted life year (QALY) gained

### Sample size

In line with IMMPACT recommendations, our primary outcome reports Sum of Pain Intensity Difference (SPID). Reductions in pain severity can be reported as either change in NRS, the pain intensity difference (PID), or as a percentage change PID (%PID). The International Association for the Study of Pain has quantified clinically meaningful improvements in pain intensity. Depending on how severe the initial pain is, clinically important improvements in PID range from 1.3 to 5.2. Those with severe pain will need to experience a greater reduction in pain than those with mild pain to experience a clinically important reduction in pain. Similarly, improvements in %PID range from 20.1 to 56.1% depending on severity of pain. Previous studies have established that improvement in PID is equivalent to improvement in SPID [39].

The study has been powered to identify change in SPID calculated using the change in PID. To ensure our study is able to detect at least a 20% improvement in %SPID, regardless of baseline pain intensity, our sample size calculation is powered to detect 20% improvement in %PID, which in turn is equivalent to a 1 point difference (0–10 NRS) in effectiveness between morphine and ketamine.

Previous randomised controlled trials comparing ketamine and morphine have adopted a standard deviation of 3.0 [35, 36, 40, 41]. A review of existing prehospital studies identified that the average non-response/withdrawal rate was 14% [40, 42–45]. We therefore calculate our sample size assuming a standard deviation of 3.0, 1:1 randomisation, a power of 90%, significance level of 5% and a withdrawal/non-response rate of 15%.

Based on these estimates we calculate our trial will require a sample of 446 subjects, recruiting 223 to each arm of the study, to detect a 1 point difference on the NRS (range 0–10) in primary outcome between morphine and ketamine.

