## Outcomes

Table 2 presents the timings of when study outcome measures will be collected. Table 3 details the definition and methods to calculate the study outcomes.

**Table 2 Tab2:** Schedule of delivery of intervention and data collection

Visit	1	2	3	4
Visit Window (No. Weeks ± No. Days)	Baseline/Pre hospital/Hospital arrival	After hospital arrival	3 m (± 2w)	6 m (± 1 m)
Trial Information	✓	✓		
Informed consent		✓		
Randomisation	✓			
Vital signs	✓			
Inclusion/exclusion criteria	✓			
Intervention	✓			
Rescue analgesia	✓			
Quality of Life—EQ-5D-5L			✓	✓
Side effects & Adverse events	✓	✓	✓	✓
Questionnaire—BPI-SF			✓	✓
Questionnaire—CSRI			✓	✓
SPID	✓			
TOTPAR	✓			
Time to perceptible analgesia	✓			
Time to meaningful analgesia	✓			
Time to peak analgesia	✓			
Duration of analgesia	✓			
Patient Global Impression of Change	✓			
Resource use	✓	✓	✓	✓

**Table 3 Tab3:** Outcome measure definitions

	Definition	Mitigations
*Primary outcome*		
Effectiveness of pain relief from randomisation to arrival at hospital as measured by Sum of Pain Intensity Difference (SPID) score (using a 0–10 numerical rating scale)	The SPID is measured using a weighted sum of the scores, as shown below: $$SPID_{n} = \mathop \sum \limits_{i - 1}^{n} \left( {T_{i} - T_{i - 1} } \right)*PID_{i}$$ *T*_*i*_ is the time in hours when observation *i* is taken *PID*_*i*_ is the difference in Pain Intensity (PI) scores from initial pain score to the pain score at time *T*_*i*_. The SPID looks to calculate the area under the curve of pain intensity different over time	
*Secondary outcomes*		
The Total Pain Relief (TOTPAR)	The TOTPAR is measured using a weighted sum of the scores, as shown below: $${TOTPAR}_{n}= \sum_{i-1}^{n}\left({T}_{i}-{T}_{i-1}\right)*{PAR}_{i}$$ *T*_*i*_ is the time in hours when observation *i* is taken *PAR*_*i*_ is the pain relief score measured as defined below on a scale of 1 to 3 We measure minimal pain relief as 1.8 (1.7–1.9) change in pain score, much pain relief as 4.0 (3.9–4.1) and very much pain relief as 5.2 (5–5.4) Percentage changes defined as 20.3 (19–21.6), 44.4 (43.2–45.6), 56.1 (53.9–58.4) respectively	
Time to Perceptible Analgesia	Perceptible pain relief is defined as a 20% change in NRS pain score from the initial pain score. The time will be taken as time of perceptible analgesia minus time of first administration	If 20% change not achieved, we will score this as perceptible analgesia not achieved

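### The sample size is set in NRS points but the primary outcome is raw SPID in point-hours over a window that differs by patient, so the stated 90% power is not established for the primary outcome

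*Protocol article*

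**What the plan says.** **Sizing.** The Sample size section takes its SD from earlier work: "Previous randomised controlled trials comparing ketamine and morphine have adopted a standard deviation of 3.0". It then calculates "assuming a standard deviation of 3.0, 1:1 randomisation, a power of 90%, significance level of 5% and a withdrawal/non-response rate of 15" per cent. The result is 446 patients, 223 per arm, and the stated purpose of that number is "to detect a 1 point difference on the NRS (range 0–10) in primary outcome between morphine and ketamine". The link from this scale to the primary outcome is one cited sentence: "Previous studies have established that improvement in PID is equivalent to improvement in SPID". The section also mentions a 20% improvement in %SPID as the aim.

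**Outcome.** The Primary outcome section gives "Effectiveness of pain relief from randomisation to arrival at hospital as measured by Sum of Pain Intensity Difference (SPID) score". Table 3 (Outcomes) defines SPID as the sum of each time step, in hours, multiplied by the PID at its end, and adds: "The SPID looks to calculate the area under the curve of pain intensity different over time". Nothing in the formula divides by total time. The Primary outcome section also says that no fixed interval was set for recording pain scores.

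**Analysis.** The Data analysis section applies linear regression to SPID, adjusting for age group, gender, weight and prior IV paracetamol. Observation time is not among the covariates. SPID is computed whenever two pain scores exist. Ambulance job cycle time appears only as a secondary resource-use outcome, and no expected journey time, SPID SD or target difference in point-hours is given.

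**The concern.** A 1-point difference with an SD of 3.0 describes a pain score difference. The analysed quantity is that difference accumulated over hours, and each patient contributes a different number of hours. A patient with a steady PID of 4 scores 1.0 if observed for 15 minutes and 4.0 if observed for 60 minutes, with the same relief. Observation time also depends on recording, because two scores are enough and the last one may precede arrival.

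Two things are at stake. First, variation in duration adds variance that the calculation does not allow for, so the power statement lacks a basis on the analysed scale. Second, interpretation: a sustained 1-point benefit is 0.5 point-hours over 30 minutes and 1.0 over 60 minutes. A SPID difference reported in point-hours therefore cannot be compared with the 1-point benchmark on which the trial was justified.

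**Working it through.** **1. The plan's own figure.** Inputs from the Sample size section: difference 1, SD 3.0, 90% power, 5% significance (two-sided reproduces the result), 15% loss.

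n per arm = 2 × (1.960 + 1.2816)² × 3.0² / 1² = 189.1. Dividing by 0.85 gives 222.5, rounded up to 223, hence 446. The arithmetic is right, on the NRS scale. Evaluable patients per arm: 446 × 0.85 / 2 = 189.55.

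**2. When the bridge from PID to SPID works.** Write SPID = T × P, where T is observed time in hours and P is the patient's time-averaged PID. If T is the same for everyone, a 1-point difference becomes T point-hours and an SD of 3.0 becomes 3.0T. The ratio stays 1/3, so power is 90% for any common T. The bridge is therefore sound for a fixed window, which this trial does not have.

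**3. When T varies.** Let T have coefficient of variation c and be independent of P, and let P have SD s and mean μ. With mean T scaled to 1, the variance of SPID in an arm is s²(1 + c²) + c²μ², and the difference between arms is still 1.

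Assumptions that are not in the document: c; means of 4 and 5 (so the average of μ² is (16 + 25)/2 = 20.5); independence of T and P; and s, because the protocol gives 3.0 no time basis.

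SD of SPID = √[s²(1 + c²) + 20.5c²]. Power is for a two-sided two-sample t test with 189.55 per arm.

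| CV of duration | SD if s = 3.0 | Power | SD if s = 2.5 | Power |
|---|---|---|---|---|
| 0.2 | √10.18 = 3.19 | 86% | √7.32 = 2.71 | 95% |
| 0.3 | √11.66 = 3.41 | 81% | √8.66 = 2.94 | 91% |
| 0.4 | √13.72 = 3.70 | 75% | √10.53 = 3.24 | 85% |
| 0.5 | √16.38 = 4.05 | 67% | √12.94 = 3.60 | 77% |

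**4. Comparison with the time-averaged outcome.** Under the same assumptions, SPID divided by observed time has about 90% power if s = 3.0 and 97% if s = 2.5, whatever the CV. Raw SPID is the weaker of the two in every row. Whether it falls below 90% depends on s and c.

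**The case against.** **The SD may be conservative.** The protocol does not say whether 3.0 is the SD of a PID at one time or of a time average. Averaging several scores per patient would normally reduce it, and a time-averaged SD of about 2.6 would keep 90% power at a CV of 0.3. This stands. A reader might infer that the trial is underpowered, but the document does not support an unconditional statement that power is below 90%.

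**Randomisation and blinding protect the comparison.** This also stands. Each patient's SPID scales with observed time, but with blinded random allocation that is mainly noise plus extra weight on long journeys. A reader might go further and infer that journey time drives the result, or that the test would produce false positives. That requires observed time to differ by arm, and nothing in the document reports or predicts such a difference. If it did differ, SPID would still measure accumulated relief; it would mislead only as a statement about how well pain was relieved.

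**The protocol offers a bridge.** The PID–SPID equivalence is cited, and the source could not be checked here. A %SPID expressed relative to a maximum over each patient's window would remove duration. But the Data analysis section analyses SPID, not %SPID, and step 2 shows that the equivalence preserves power only under a common observation time. This part of the objection does not rescue the statement.

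**Changing the primary outcome would be costly.** Table 1 lists 362 of 446 patients already recruited. SPID is the registered outcome, and the section chose it to follow published recommendations. A time-averaged PID also still depends on the window, since short journeys capture mostly onset of effect. A reader might conclude that raw SPID must be replaced as primary; that is a debatable change of estimand and is not required.

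**Conclusion.** The point holds as a mismatch of scale. The number 446 is correct for 1 NRS point with an SD of 3.0, but the primary outcome is in point-hours over a window that varies by patient and is neither divided out nor adjusted for. The claim of 90% power for 1 NRS point in the primary outcome is not established, and the SPID result cannot be read directly against the 1-point benchmark.

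The size of the effect cannot be determined from the document. For duration CVs of 0.2 to 0.5 it ranges from 86% down to 67% power if the time-averaged SD is 3.0, and from 95% down to 77% if it is 2.5. These ranges rest on assumed CVs, mean PID of 4 versus 5, and duration independent of PID.

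**What to change.** Before allocation is linked to outcome data:

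- Restate the target difference and the power in point-hours, using the blinded pooled SD of SPID and the observed durations.
- Remove the statement that 90% power applies to 1 NRS point in the primary outcome.
- Pre-specify the time-weighted mean PID, SPID/(Tₙ − T₀), in NRS points, as a key supportive analysis of the primary outcome, read against the 1-point benchmark.
- Report observed duration by arm, so that a reader can see whether a SPID difference could reflect time rather than relief.

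The Data analysis section says that a detailed analysis plan goes to the Data Monitoring Committee for approval before final analysis, so these changes can be made there with a short protocol clarification. The cost is a little more analysis and a possibly less favourable power figure. No patients are added and the registered primary outcome stays as it is.

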### Data analysis

The statistical analysis will follow the estimand framework [46]. Primary analysis will be by intention to treat. The primary outcome will be the SPID, a measure of the area under the curve of the pain score difference from baseline over time. The primary outcome will be analysed using a linear regression. Both unadjusted and adjusted (for important covariates) estimates and 95% confidence intervals for the treatment effect will be obtained. The adjusted estimates will form the basis for the primary analysis. Descriptive summaries of the outcomes will be presented as frequencies or means and medians. For the adjusted estimates, the covariates used will be age (< 60; ≥ 60 years), gender, weight and alternative parenteral IV paracetamol prior to randomisation (as a dichotomy split by yes or no). Age and gender have been chosen as covariates as these groups can experience pain differently, administration of IV paracetamol prior to randomisation is included as a covariate as it is an adjunctive treatment that may impact pain response. Weight is included as a covariate since different weight groups have different requirement for an adequate dose of IMP. For continuous secondary outcomes, analysis will be carried out in a similar way to the primary outcome. For categorical outcomes, logistic regression models will be used. Participant vital signs are recorded in a longitudinal format, for these outcomes we will use a mixed effect model.

Various intercurrent events have been identified for this trial, in line with the estimand framework [46], and approaches to dealing with these have been considered. For discontinuation of the allocated treatment and use of rescue analgesia, we will follow the treatment policy, where the data is analysed as observed. Compliance with administration of the trial drug as per the trial protocol will be monitored. If there is a noticeable degree of non-compliance, we will carry out a complier average casual effects (CACE) analysis [47, 48]. If sufficient data permits, sensitivity analysis will be conducted on a modified intention to treat population, excluding participants that were randomised but the drug was not given. Again, if sufficient data permits, participant deaths will be analysed using Pocock’s win ratio method, this allows death to be interpreted as a participant outcome and infer if the intervention is significantly better than the standard care having considered the clinical priority.

Item missingness is expected for the primary outcome due to the method of recording data used in the trial, however the primary outcome is a measure of the area under a curve, therefore if two pain measurements are recorded the primary outcome can still be measured. Imputation methods have been considered for missingness, but methods such as last observation carried forward are not reliable due to the variability of pain scores, and we cannot assume that pain scores are missing at random therefore multiple imputation is also not feasible. Analyses and template tables will be reported in a detailed statistical analysis plan for review and approval by the Data Monitoring Committee (DMC), prior to final statistical analysis of the data.

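### The primary SPID model leaves out the initial pain score, which gives up a little precision and leaves chance baseline imbalance uncorrected

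*Protocol article*

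**What the plan says.** The Data analysis section states that "The primary outcome will be analysed using a linear regression" and that "The adjusted estimates will form the basis for the primary analysis". It then names the covariates: age, split at 60 years, followed by "gender, weight and alternative parenteral IV paracetamol prior to randomisation (as a dichotomy split by yes or no". A reason follows for each of the four, so this reads as a closed list and not as an example to be completed later. No other section adds the initial pain score.

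The outcome is described there as "a measure of the area under the curve of the pain score difference from baseline over time". Table 3 gives the building block: PID at each time "is the difference in Pain Intensity (PI) scores from initial pain score to the pain score at time".

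The Eligibility criteria require an NRS score of at least 7 and exclude patients who cannot use the scale. Under Allocation sequence and randomisation, packs are blocked by site batch order, with no stratification on pain score.

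**The concern.** The initial score enters every PID term of the outcome, and it caps the largest fall a patient can show: 10 points from a start of 10, 7 points from a start of 7. Taking a change score does not replace adjusting for baseline. It fixes the baseline coefficient in advance instead of estimating it, so some baseline-related variance stays in the residual unless change happens to be unrelated to the starting score.

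Two things follow. The confidence interval is somewhat wider than it need be. And if one arm starts by chance with more pain than the other, part of that difference passes into the treatment estimate. Neither the randomisation nor the listed covariates correct for this.

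**Working it through.** **Inputs from the article (Sample size).** Difference 1 NRS point, SD 3.0, 1:1 allocation, power 90%, significance level 5% (taken as two-sided), loss 15%, total 446.

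**Reproducing the plan's figure.** n per arm = 2 × [3.0 × (1.960 + 1.282)]² / 1² = 189.13. Dividing by 0.85 gives 222.51, rounded up to 223 per arm, or 446. The stated figure is reproduced with the full SD of 3.0, so it counts on no covariate gain.

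**Reference power.** Evaluable per arm = 223 × 0.85 = 189.55. SE = 3.0 × √(2/189.55) = 0.308. Power for 1 point is 90.1% and the 95% CI half-width is 0.604.

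**What correlation is plausible?** The article gives none. With r the correlation of PID with the initial score, given the covariates already in the model, r = slope × SD(baseline) / 3.0. Scores confined to 7–10 have an SD of at most 1.5 (half the patients at each end), and about 1.12 if uniform. A slope of 0 means change is unrelated to baseline. A slope of 1 means later pain is unrelated to starting pain.

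| Assumed baseline SD | r at slope 0.3 | r at slope 0.5 | r at slope 1.0 |
|---|---|---|---|
| 1.0 | 0.10 | 0.17 | 0.33 |
| 1.12 | 0.11 | 0.19 | 0.37 |
| 1.5 | 0.15 | 0.25 | 0.50 |

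The working range is therefore r = 0.1 to 0.3. An r of 0.4 would need a slope of 0.4 × 3.0 / 1.118 = 1.07 with uniform scores, or 0.8 even at the maximum SD.

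**Gain from adjusting.** Residual SD = 3.0 × √(1 − r²). The equivalent number of extra evaluable patients is 379.1/(1 − r²) − 379.1.

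| r | Variance cut | Residual SD | Power | CI half-width | Extra patients |
|---|---|---|---|---|---|
| 0 | 0% | 3.000 | 90.1% | 0.604 | 0 |
| 0.1 | 1% | 2.985 | 90.3% | 0.601 | 4 |
| 0.2 | 4% | 2.939 | 91.2% | 0.592 | 16 |
| 0.3 | 9% | 2.862 | 92.5% | 0.576 | 37 |

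**Chance imbalance.** The 95% limit for the between-arm difference in initial score is 1.96 × SD × √(2/189.55): ±0.20 at SD 1.0 and ±0.30 at SD 1.5. Multiplying by slopes of 0.3 to 1.0 gives shifts from 0.20 × 0.3 = 0.06 to 0.30 × 1.0 = 0.30 points. The top figure combines the largest possible SD with a slope of 1 (r = 0.5). Within r = 0.1 to 0.3 the shift is r × 0.604, or 0.06 to 0.18 points.

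**Scale.** These figures are in NRS points, as in the sample size section. SPID is in point-hours over a journey of variable length, and duration adds variance that the initial score cannot explain. As an illustration, assume PID with mean 4 and SD 3, and an independent duration with mean 1 h and SD 0.4 h. Then Var(SPID) = 9 × 1 + 0.16 × 16 + 9 × 0.16 = 13.0. The variance cut is multiplied by 9/13 = 0.69, so 1–9% becomes about 0.7–6%.

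**The case against.** The best defence is that nothing is broken. Under randomisation the estimate without the initial score is unbiased on average, and the 446 stands without any help from covariates. The restricted entry range keeps the gain small, and SPID's variable duration probably makes it smaller. All of that stands, and it limits the point to efficiency and protection against chance imbalance.

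A reader might take the Sample size section as the article's own admission that starting pain predicts relief. It does not go that far. "Depending on how severe the initial pain is, clinically important improvements in PID range from 1.3 to 5.2" and "Those with severe pain will need to experience a greater reduction in pain than those with mild pain" concern how large a fall must be to matter to the patient, not how large a fall to expect. Nor does any figure show that the initial score is the strongest available predictor. The 10-versus-7 ceiling bounds the possible fall without giving the expected one.

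A reader might also want the complaint widened to the split of age at 60, or to every secondary outcome derived from the NRS. The article gives no figure from which a loss due to the age split could be computed, so that is a modelling preference. Times to perceptible and meaningful analgesia are already defined by percentage change from the initial score, which partly scales for baseline.

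The defence does not remove the core. The list is fixed in the article with reasons, the omitted score is part of the outcome's own definition, and using it needs no new data.

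**Conclusion.** The point holds as a modest improvement that should be made, not as an error that invalidates the analysis. For an assumed r of 0.1 to 0.3, the omission costs 1% to 9% of the information on the PID scale, a difference of 0.2 to 2.4 percentage points of power. A chance imbalance at its 95% limit could move the estimate by 0.06 to 0.30 points against the 1-point target, and the upper end needs extreme assumptions.

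The fact of the omission is certain from the text. Its size is not: it rests on an assumed correlation, baseline SD and slope, and on NRS-point figures that are only indicative for SPID. A reader might infer that the treatment estimate is biased or the trial underpowered. The documents support neither. The shift is conditional on the arms differing by chance, and planned power is met without the covariate.

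**What to change.** In the primary adjusted SPID model, add the initial (pre-treatment) NRS score as a continuous covariate, and keep the current four-covariate model as a sensitivity analysis. Write this into the statistical analysis plan before any unblinded analysis. The timing matters because the Blinding section lets the statistician link pack number to allocation, so a covariate added after results are seen would be open to challenge. If the plan already contains this covariate, only the article's list needs reconciling with it.

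The cost is one line of text and one model parameter. No new data are needed: the score is an entry requirement, and SPID cannot be computed without it. At the time of the article 362 of 446 patients had been recruited, and the analysis plan was still to go to the Data Monitoring Committee for approval, so the change could still be pre-specified.

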Time to Meaningful Analgesia	Defined as a 44% change in NRS pain score from initial pain score. The time will be taken as time of meaningful analgesia minus time of first administration	If 44% change not achieved, we will score this as meaningful analgesia not achieved
Time to Peak Analgesia	Measured as the time when lowest NRS pain score, relative to initial pain score, is achieved minus time of first administration	
Duration of Analgesia	Measured as the time period in which patient pain scores have consecutively decreased or remained stationary (There may be different instances of this per patient)	
Requirement for Rescue Analgesia	We will record whether a patient has needed rescue analgesia and which analgesia was administered, Entonox, paracetamol, ibuprofen, or other	
Proportion of patients with pain intensity score below 4/10 on NRS scale	At hospital arrival the research paramedic will record a NRS pain score. We will provide the proportion, as a percentage, of each patient that achieved a score < 4/10	If there is no hospital arrival score, we will use the scores recorded in the ambulance journey
Vital Signs	At each observation time, the respiratory rate (bpm), oxygen saturations (%), heart rate (bpm), blood pressure (mmHg) and their Glasgow Coma Scale (GCS)	
Glasgow Coma Scale	Three subscales measuring eyes, verbal, and motor response of each patient. The scales are as such: Eyes 1–4 Verbal 1–5 Motor 1–6	
Global Impression of Change	Using a 7-point Likert scale. The options offered ranging from ‘very much improved’ to ‘very much worse’	
Side effects and adverse events	Measured in the following categories, ‘Airway’, ‘Respiratory’, ‘Cardiovascular’, ‘Neurologic’, and ‘other’	
Ambulance job cycle time	Time taken from arrival on scene to hospital arrival	
Number of ambulance resources	Number of doctors, paramedics, doctors, and vehicles attending scene	
Cumulative IMP doses administered	Total dose of IMP administered	
CT scan use	If patient had a CT scan and how many	
Hospital or ICU admission	Yes; no option if patient is admitted to hospital or ICU	
Length of stay in ED, ICU, or hospital	Classed as date and time of admission to date and time of discharge	
BPI-SF at 3 and 6 Months		

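### No model named in the plan suits times to perceptible and meaningful analgesia that some patients never reach; linear regression of these times can use achievers only and can miss a real benefit

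*Protocol article*

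**What the plan says.** In the protocol article, Table 3 (Outcomes) defines time to perceptible analgesia as the interval from first administration to a 20% change in the pain score, and time to meaningful analgesia as the interval to a 44% change. The table's mitigations column covers patients who do not get there: "If 20% change not achieved, we will score this as perceptible analgesia not achieved" and "If 44% change not achieved, we will score this as meaningful analgesia not achieved". Neither row gives such a patient a time.

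The Data analysis section assigns models by type of outcome. For SPID, "The primary outcome will be analysed using a linear regression". For the rest, "For continuous secondary outcomes, analysis will be carried out in a similar way to the primary outcome". Categorical outcomes go to logistic regression and vital signs to a mixed-effects model. The win ratio is mentioned only for deaths. No time-to-event, censoring or rank-based method is named for the two onset times. The paragraph on missing data concerns pain scores for the primary outcome, not onset times that do not exist.

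Under Trial design and setting, the prehospital phase ends at hospital arrival, so the length of observation differs between patients.

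**The concern.** An elapsed time is neither categorical nor a vital sign, so the one stated rule that fits it is linear regression. A patient without a time contributes nothing to that regression. The comparison is then between patients who reached the threshold in each arm. Reaching it is a response to treatment, so these are no longer the groups that randomisation formed.

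Non-achievers are also not ordinary missing data. They are known not to have reached the threshold up to their last score or hospital arrival, which is right censoring at a patient-specific time. Discarding them loses that information.

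The Background and Trial rationale sections give rapid onset as a reason to study ketamine, and these two outcomes measure it directly. If one drug brings more patients to relief, and sooner, an achievers-only mean can show little of it.

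**Working it through.** **The plan's own figure.** The article states no figure for the onset times. Its sample size gives a plausible number of evaluable patients. The inputs, from Sample size, are: "assuming a standard deviation of 3.0, 1:1 randomisation"; "a power of 90%, significance level of 5% and a withdrawal/non-response rate of 15" per cent; and the aim "to detect a 1 point difference on the NRS (range 0–10) in primary outcome between morphine and ketamine". Taking the test as two-sided (sidedness is not stated):

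- n per arm = 2 × 3.0² × (1.960 + 1.282)² / 1² = 189.1, so 190 evaluable per arm
- 189.1 / 0.85 = 222.5, so 223 per arm and 446 in total

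This agrees with "we calculate our trial will require a sample of 446 subjects, recruiting 223 to each arm of the study".

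**Illustration 1: a benefit that is missed.** Assumed, because the article gives no such figures: constant hazard, every patient observed for c = 45 min, 190 per arm, 50% achieving on morphine, true hazard ratio 1.5 in favour of ketamine.

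- Hazards: L0 = ln 2 / 45 = 0.01540 and L1 = 1.5 × L0 = 0.02310 per minute
- Achieving by 45 min: 1 − e^(−L0c) = 50% and 1 − e^(−L1c) = 64.6%, i.e. 95 and about 123 achievers
- Median time over all patients: ln 2 / L = 45 and 30 min
- Mean among achievers, 1/L − c·e^(−Lc)/(1 − e^(−Lc)): 64.9 − 45.0 = 19.9 min and 43.3 − 24.6 = 18.7 min
- SD among achievers, √[1/L² − c²·e^(−Lc)/(1 − e^(−Lc))²]: 12.8 and 12.6 min
- Linear comparison: SE = √(12.8²/95 + 12.6²/123) ≈ 1.74; z = 1.25/1.74 ≈ 0.72; power ≈ 11%
- Log-rank, about 218 events: z = ln 1.5 × √(218/4) ≈ 2.99; power ≈ Φ(2.99 − 1.96) ≈ 85%
- Proportions achieving: z = 0.146/√(0.50 × 0.50/190 + 0.646 × 0.354/190) = 0.146/0.0502 ≈ 2.92; power ≈ 83%

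The same steps with other achievement rates on morphine:

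| Achieving on morphine | Linear, achievers only | Achieved or not, all patients | Log-rank, all patients |
|---|---|---|---|
| 40% | 8% | 76% | 77% |
| 50% | 11% | 83% | 85% |
| 60% | 17% | 87% | 90% |

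In the 50% case a 15-minute difference in median time shrinks to 1.2 minutes among achievers. The direction stays correct.

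**Illustration 2: when the direction could change.** Simulation of 3,000 trials per scenario, 223 per arm, with lognormal times (log-SD 0.6; half that for late responders). The median is 15 min, or 10 min in the last row. The all-patient test is a rank test with non-achievers ranked worst.

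| Achieving (better v other arm) | Extra achievers' median time | Better arm's mean among achievers | Significant in wrong direction, achievers only | All-patient rank test favours better arm |
|---|---|---|---|---|
| 70% v 50% | 15 min (as others) | no difference | 2% (4.5% either way) | 96% |
| 70% v 50% | 30 min | 3.8 min slower | 71% | 70% |
| 70% v 50% | 40 min | 6.8 min slower | 97% | 57% |
| 80% v 60% | 30 min | 3.4 min slower | 67% | 57% |
| 90% v 80% | 25 min | 1.6 min slower | 44% | 9% |

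Reversal appears only where the additional achievers are assumed to respond late.

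**The case against.** The article never lists the onset times as continuous outcomes and never says that non-achievers are dropped. Both are inferences from its general rules. The mitigations column shows that non-achievers were considered: they receive a category, and categorical outcomes go to logistic regression. On that reading achievement would be compared in everyone, and in Illustration 1 this has 83% power against 85% for the log-rank test. An analysis plan that is not shown may also set a different model for these outcomes.

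Much of this stands. It removes any claim that the plan must overlook a difference in response, and it makes the 11% a statement about the time comparison alone. It does not rescue that comparison. Logistic regression of achievement says nothing about how soon relief came, which is the named outcome. Nor is this only detail deferred to an analysis plan: the article fixes a rule by outcome type and a scoring rule for non-achievers, and the two do not work together.

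A reader might go further and infer that the planned analysis will reverse a true benefit. The documents do not support that. The direction is correct throughout Illustration 1, and reversal in Illustration 2 needs late extra responders, on rates and times that the article does not report.

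**Conclusion.** The point holds for two secondary outcomes. The stated rules leave linear regression as the only fit for these times, and it can use only achievers, who are selected after randomisation. A real benefit in speed of onset can be missed: about 8% to 17% power against 77% to 90% for a log-rank test, under a constant hazard, a fixed 45-minute window, 190 per arm, a hazard ratio of 1.5 and 40% to 60% achievement on morphine. A result in the wrong direction is possible but depends on assumed late responders. A logistic analysis of achievement would recover most of the power without analysing time. The SPID analysis and the sample size are untouched. The change is worth making before final analysis.

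**What to change.** State in the analysis plan, for both outcomes:

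- Time-to-event analysis of all randomised patients, by Cox regression with the primary-model covariates and Kaplan-Meier curves.
- The time origin, including the rule for patients randomised but not given the drug, since Table 3 counts from first administration.
- Censoring of non-achievers at the last recorded score or hospital arrival, with one of the two chosen in advance.
- Handling of death, and of rescue analgesia by treatment policy, as the Data analysis section already does for intercurrent events.
- An interval-censored analysis, because the Primary outcome section sets no fixed scoring interval.
- A comparison of the proportion achieving each threshold in all randomised patients.

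The cost is wording and some programming. The times are already needed for the outcome definitions, and no extra patients are required.
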